### **3.7 Visit 3**

The participants are recommended not to conduct intense physical activity or drink alcohol 24 h before the visit. They should be fasting since midnight. Nicotine users should not have used nicotine the same day.

The following procedures will be done at visit 3:

- ID is checked
- The participant returns any remaining doses. The number of remaining doses are noted and the participant's dosing document is collected.

- Any changes in medication are reported.
- Adverse events are noted, and appropriate follow-up is initiated.
- Any remaining capsules are returned for destruction.
- Participants leave their stool sample
- Length, weight, and waist-hip circumference are measured.
- Venous fasting blood samples are drawn for analysis of fasting blood glucose, HbA1c, insulin, c-peptide, Hb, GT, lipid levels (HDL, LDL, total cholesterol, triglycerides), TSH and free fatty acids. Total blood volume is estimated to 25 mL.
- Participants complete a questionnaire on dietary habits, physical activity, smoking and alcohol habits.
- A note is made in the medical record about the visit.
- Study is finished for the participant.

### **3.8 Questionnaire**

The questionnaire at visit 2 and 3 will assess the following:

- Physical activity using the short IPAQ (international physical activity questionnaire), which is a commonly used scale to assess physical activity.
- Dietary habits using items that have been validated in Stockholm health questionnaire 2010 (Stockholms folkhälsoenkät 2010).
- Tobacco and alcohol, by validated items previously used by the national Health questionnaires in Sweden (Folkhälsoinstitutets nationella folkhälsoenkäter).

### **3.9 Number of participants**

100 participants will participate in the study; 50 will receive BSE and 50 placebo.

### **3.10 Time plan**

Aug 2018-Dec 2020

## **4. STUDY VARIABLES**

### **4.1 Primary objective**

The primary objective with the study is to test the hypothesis that BSE with standardized amounts (at least 150  $\mu$ mole per daily intake) of sulforaphane, improves fasting blood glucose using intraindividual comparisons before and after treatment in the BSE relative to the placebo group.

### **4.2 Secondary objectives**

The secondary objectives are to study the effect of BSE on the secondary effect variables, HbA1c, fatty liver index, fasting lipids, free fatty acids, insulin secretion, HOMA-IR and weight using intraindividual comparisons before and after treatment in the BSE relative to the placebo group.

### **4.3 Effect variables**

#### **The primary effect variable:**

Venous fasting blood glucose. Venous fasting blood glucose will be analysed at screening visit (only participants having capillary glucose 6.0-6.9 mmol/l), visit 2 and 3 and used for effect analyses.

#### **Secondary effect variables include:**

- HbA1c
- a fatty liver index based on BMI, waist circumference, triglycerides and GT (Gastaldelli et al., 2009)
- fasting lipids, free fatty acids, insulin secretion
- HOMA-IR, based on fasting glucose and insulin
- Weight
- We will later analyse stool samples to investigate changes in abundance of bacterial strains between the BSE and placebo groups

## **5. STUDY COMPOUND**

### **5.1 BSE**

The study product is BSE with standardized amounts of sulforaphane. BSE contains a mixture of maltodextrin as a bulking agent and copper chlorophyllin (E 141) as a food additive. BSE is a dried powder of an aqueous extract of broccoli sprouts that provides a consistent and stable source of sulforaphane. A mixture of maltodextrin and copper chlorophyllin will be used as placebo. The active compound and the placebo are the same except BSE. The placebo will look similar to the BSE-containing mixture. Placebo or BSE powder will be provided as dry mixtures in sealed, non-transparent portion size bags. Each BSE bag contains 150  $\mu$ mole, equal to 0.26 g, sulforaphane at a minimum. The mixtures are suspended with appr. 1 dl water and are ingested once daily in the morning. BSE should be stored at room temperature in dry conditions.

The doses of sulforaphane contained in the BSE is not possible to get by eating fresh broccoli, thus it has to be given as an extract.

### **5.2 Packing**

Lantmännen will provide the dry mixtures with BSE or placebo as portion size bags. The bags are non-transparent and look similar between BSE and placebo. The mixtures will be ready to mix with liquid (e.g. water).

### **5.3 Randomization**

Lantmännen will manufacture 60 kits with BSE and 60 with placebo and send to the assigned pharmacy in Göteborg. These kits will be divided into BSE or placebo so that it is obvious for the pharmacy what each kit contains. The randomization will be organized via Gothia Forum using a computer-based block randomization algorithm. Gothia Forum will send the randomization list in sealed envelopes to the local pharmacy, where each kit will then be marked with a number from 1 to 120 (corresponding to the study IDs). The local pharmacy will ensure that the kit marked 1 is BSE or placebo based on the randomization list.

Each participant receives the kit that corresponds to his/her study ID. The randomization is blind to both participants and the Investigator during the study. After the study, the participants have the right to know, upon asking, whether they received BSE or placebo.

The randomization list is kept with the local pharmacy during the entire study. Sealed envelopes with randomization information for each participant are sent to investigator and may be opened in case of emergency.

The randomization list will be sent to [name] after the study to enable data analysis.

#### **5.4 Compliance**

The participants should return any remaining capsules at visit 3. Only participants who have taken >75% of their capsules during the total study period and >80% during the last month will be included in the per protocol analyses. This is calculated by (the number of delivered bags – number of returned bags) / number of days in the study.

#### **5.5 Reimbursement**

Participants will receive travel reimbursement. This amount is subject to tax.  
Participants will receive the payment into their bank account at the end of the study.

## **6. STATISTICS AND DATA HANDLING**

### **6.1 Statistics**

The primary effect variable is venous fasting blood glucose. Participants will be analysed using intraindividual one-tailed comparisons before and after treatment and compared between the placebo and BSE arms using Student's t-test. The study hypothesis is that participants taking BSE for 12 weeks will have at least 0.3 mM lower fasting blood glucose on average than participants taking placebo. The intra-individual standard deviation of fasting blood glucose is 0.63 mM, based on analyses in our longitudinal cohorts of subjects with impaired fasting blood glucose. We therefore need 37 participants in each randomization group to detect a difference of 0.3 mM in fasting blood glucose between the groups at 80% power at  $p < 0.05$ . We aim to recruit 50 participants in each group to cover for potential dropouts.

We will also make a subgroup analysis of participants with fasting triglycerides above median. This is based on our previous study on BSE (Axelsson et al.) showing that BSE is particularly effective in individuals with increased triglyceride levels. It is known that increased triglycerides are more common in subjects with elevated fatty liver content (Gastaldelli et al., 2009) and we therefore want to investigate whether this subgroup of the population would benefit more from BSE.

Both Intention-to treat (ITT) and per protocol (PP) analysis of the outcome variables will be performed and ITT will be used as a basis for the conclusions. Missing values will be replaced by the latest value available. Participants with poor compliance (see 5.4) will however not be included in any analyses.

The secondary study variables, HbA1c, fatty liver index, fasting lipids, free fatty acids, insulin, HOMA-IR and weight, will be analysed using intraindividual comparisons between visit 2 and 3.

We will later analyse stool samples to investigate changes in abundance of bacterial strains between the BSE and placebo groups.

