- Venous fasting blood samples are drawn for analysis of glucose, creatinine, ASAT, ALAT, GT, ALP, bilirubin, PK, thrombocytes. Total blood volume is estimated to 25 mL.
- If venous fasting blood glucose is above or equal to 6.1 mmol/l and below 7.0 mmol/l, the participant is scheduled for visit 2, which will be 1-14 days after

the screening visit.

- They receive a tube for stool sampling and are instructed how to sample.

### 3.4 Visit 2

Participants who are eligible to participate will be scheduled for a second visit 1-14 days after their first visit. If the venous analyses from the screening visit of creatinine, ASAT, ALAT, GT, ALP, bilirubin, PK, thrombocytes, show clinically relevant abnormalities that upon decision by PI precludes participation, that the subject's visit 2 will be cancelled.

The participants are recommended not to conduct intense physical activity or drink alcohol 24 h before the visit. They should be fasting since midnight. Nicotine users should not have used nicotine the same day.

The following will be done at visit 2:

- ID is checked
- Information on current use of pharmaceutical drugs is collected
- Venous fasting blood samples are drawn for analysis of fasting glucose, HbA1c, insulin, c-peptide, Hb, GT, lipid levels (HDL, LDL, total cholesterol, triglycerides), TSH and free fatty acids. Total blood volume is estimated to 25 mL.

If venous fasting blood glucose is 6.1-6.9 mM the individual can be included in the study and we proceed with the following:

- For women of fertile age we make a pregnancy test and proceed with the remaining points only if that is negative.
- The participant receives a study ID, using consecutive numbers and are randomized to receive BSE or placebo (see point 5.3 Randomization)
- Length, weight, and waist-hip circumference are measured.
- Participants complete a questionnaire on dietary habits, physical activity, smoking and alcohol habits.
- Participants leave their stool sample
- A note is made in the medical record about the visit.
- Study subjects receive their study medication (BSE or placebo) to bring home
- They receive a tube for stool sample to be sampled before visit 3

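### The primary analysis is an unadjusted t-test on change with no named baseline reading; ANCOVA on both pre-treatment glucose values is a modest gain in precision that needs no new data

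*Protocol*

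**What the plan says.** Section 6.1 fixes the primary test: "intraindividual one-tailed comparisons before and after treatment and compared between the placebo and BSE arms", by Student's t-test. Section 4.1 states the same contrast, namely that BSE "improves fasting blood glucose using intraindividual comparisons before and after treatment in the BSE relative to the placebo group". Neither section mentions a baseline covariate.

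Three venous glucose values exist per participant. Section 4.3 says that glucose is measured at screening, "visit 2 and 3 and used for effect analyses". It does not say how the screening value enters the comparison. For the secondary variables section 6.1 names visits 2 and 3; for the primary variable it names no starting visit.

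Entry is restricted twice. Section 3.3 requires a venous value of at least 6.1 and below 7.0 mmol/l at screening. Section 3.4 then applies the window again: "If venous fasting blood glucose is 6.1-6.9 mM the individual can be included in the study".

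The design target is "at least 0.3 mM lower fasting blood glucose on average than participants taking placebo", with an intra-individual SD of 0.63 mM, 80% power and p < 0.05. This gives 37 per group, and 50 per group are to be recruited. No correlation between baseline and follow-up is given.

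**The concern.** Subtracting the baseline uses it with full efficiency only if visit-3 glucose follows it with a slope of 1. In this trial the baseline is squeezed into a window of less than 1 mM at two visits, so much of its remaining spread is day-to-day variation. Subtracting it then adds noise that a fitted slope would avoid.

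The unnamed baseline is a separate gap. Change from screening, from visit 2 and from their mean are three different estimates with different precision, and the text permits all three. For a single primary endpoint that choice should be closed before unblinding.

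**Working it through.** **1. The plan's own figure.** For two arms, n = 2(z_α + z_β)²(σ/δ)², with σ = 0.63 and δ = 0.3 (section 6.1), so (σ/δ)² = 4.41.
- One-sided: 2 × (1.645 + 0.842)² × 4.41 = 54.5, so 55 per arm.
- Two-sided: 2 × (1.960 + 0.842)² × 4.41 = 69.2, so 70 per arm.
- The stated 37 matches only a two-sided one-sample (paired) t-test (36.6, rounded up), not the comparison described.
- With 50 per arm and no dropout, the change-score t-test has power 0.77 one-sided and 0.66 two-sided.

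**2. Gain from adjusting for visit 2 alone, taking 0.63 as the SD of change.** Residual variance = Var(change) − s0²(1 − b)², where s0 is the baseline SD and b the slope of visit 3 on visit 2. Assumption: baseline uniform over 6.1 to 7.0, so s0 = 0.9/√12 = 0.26.

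| b (assumed) | Variance ratio | n per arm, one-sided (two-sided) | Power at 50 per arm, one-sided (two-sided) |
|---|---|---|---|
| 0 | 0.83 | 46 (58) | 0.83 (0.74) |
| 0.2 | 0.89 | 49 (62) | 0.81 (0.71) |
| 0.4 | 0.94 | 52 (65) | 0.79 (0.69) |
| 0.6 | 0.97 | 54 (68) | 0.78 (0.68) |

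**3. Simulation of the double selection.** Each person has a stable true level plus independent within-person error. Those with both readings from 6.1 to below 7.0 are kept. The between-person SD and population mean are assumptions. The within-person SD is 0.63 if the protocol's figure describes one reading, or 0.63/√2 = 0.445 if it describes a change; 0.30 is added as a low value. The population mean is 5.8 mM (5.7 in the first row). Power is one-sided at 50 per arm for 0.3 mM.

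| Within SD | Between SD | Slope | SD, change from visit 2 | SD, change from mean of both | SD, ANCOVA on both | Variance cut vs visit 2 | Cut vs mean | Power, change from visit 2 → ANCOVA |
|---|---|---|---|---|---|---|---|---|
| 0.30 | 0.5 | 0.53 | 0.386 | 0.359 | 0.358 | 14% | 0.6% | 0.987 → 0.994 |
| 0.445 | 0.3 | 0.24 | 0.528 | 0.503 | 0.496 | 12% | 3% | 0.884 → 0.916 |
| 0.445 | 0.5 | 0.40 | 0.546 | 0.522 | 0.519 | 10% | 0.9% | 0.865 → 0.893 |
| 0.445 | 0.7 | 0.47 | 0.556 | 0.532 | 0.531 | 9% | 0.3% | 0.853 → 0.881 |
| 0.63 | 0.3 | 0.17 | 0.709 | 0.688 | 0.677 | 9% | 3% | 0.681 → 0.716 |
| 0.63 | 0.5 | 0.29 | 0.738 | 0.717 | 0.713 | 7% | 1.3% | 0.651 → 0.677 |
| 0.63 | 0.7 | 0.38 | 0.756 | 0.736 | 0.734 | 6% | 0.5% | 0.633 → 0.655 |

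Wider runs (between-person SD 0.4-0.6, population mean 5.5-6.0, within-person SD 0.25-0.63) gave slopes of 0.22-0.63. The cuts were 5-10% with visit 2 alone and 6-17% with both readings. Cuts of 13-17% occurred only at within-person SD 0.25-0.30.

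**4. Chance imbalance.** The SE of the baseline difference at 50 per arm is 0.26 × √(2/50) = 0.052 mM. It moves the change-score estimate by (1 − b) times that: 0.042 mM at b = 0.2 and 0.021 mM at b = 0.6.

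**The case against.** The strongest reply is that nothing here is an error. A t-test on change is unbiased and valid under randomization whatever the slope; it does not assume a slope of 1. Sections 4.1 and 6.1 agree on the contrast. This stands: the point concerns efficiency and an unnamed baseline.

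The second reply is that the gain depends on the comparator. If section 4.3 means that both pre-treatment readings form the baseline, a change from their mean already captures nearly all of it. ANCOVA then adds about 0-2% (about 3% at a between-person SD of 0.3). This also stands. It is equally a reason to say which reading is meant, because change from visit 2 is the natural reading by analogy with the secondary variables.

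A reader might join the 17% upper figure (50/0.83 = 60, so ten participants per arm) to the shortfall in power. The two do not occur together. The largest cuts arise where power is already about 99%; at a within-person SD of 0.63, where power is low, the cut is 6-9%. A reader might also infer that ANCOVA removes a serious imbalance. It adjusts for imbalance, and the entry window already keeps the imbalance small. Nor does the plan propose to claim efficacy from within-arm tests: sections 4.1 and 4.2 define effects relative to placebo.

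**Conclusion.** The point holds as a modest, free improvement plus a definition to supply. Compared with change from visit 2, ANCOVA on both readings saves about 6-10% of residual variance at within-person SDs of about 0.45-0.63. That equals roughly three to six participants per arm (50/0.94 = 53; 50/0.90 = 56), or 2-3 points of one-sided power. The saving reaches 12-13% if the between-person SD is only 0.3 and the within-person SD 0.445, where the change score already has power of about 0.88.

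The direction is secure whenever the slope is below 1. The size rests on assumed variance components and on true levels that stay put over 12 weeks. Independent drift would enlarge the variance of change and shrink the percentage. ANCOVA does not rescue 37 per group: in the table for visit 2 alone, the one-sided requirement stays at 46-54.

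**What to change.** In section 6.1, state the primary analysis as visit-3 venous fasting glucose by ANCOVA with arm, visit-2 glucose and screening glucose as covariates, reporting the adjusted between-arm difference with its 95% CI. Name visit 2 as baseline wherever a change in the primary variable is reported, and make section 4.3 say that the screening value enters as a covariate. Use the same model with the visit-2 value for each secondary variable.

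The cost is wording in the protocol or SAP before unblinding and one or two of about 98 degrees of freedom. No extra visit, sample or participant is needed. The sample-size calculation must be corrected separately.

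### The stated 37 per group does not give 80% power for the planned between-arm t-test: if 0.63 mM is the SD of change, power is 52% (two-sided) or 65% (one-sided) at 37 per arm, and 65% or 76% at the full 50

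*Protocol*

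**What the plan says.** Protocol section 6.1 describes the primary analysis as "intraindividual one-tailed comparisons before and after treatment and compared between the placebo and BSE arms", by Student's t-test. Section 4.1 sets the same contrast: the before-after change on BSE relative to the change on placebo. The hypothesis in 6.1 is that BSE participants "will have at least 0.3 mM lower fasting blood glucose on average than participants taking placebo". The variability input is "The intra-individual standard deviation of fasting blood glucose is 0.63 mM", attributed to the sponsor's own longitudinal cohorts. From these figures, with 80% power and p < 0.05, the section concludes "We therefore need 37 participants in each randomization group to detect a difference of 0.3 mM in fasting blood glucose between the groups". It then adds "We aim to recruit 50 participants in each group to cover for potential dropouts" and gives no dropout rate. Sections 2 and 3.9 confirm 50 per arm.

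No correlation between baseline and follow-up, no covariate adjustment and no other variance reduction is stated.

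**The concern.** The sample-size sentence claims a power for the difference between two independent arms. The variance of that difference is the sum of the two arms' variances, twice that of a single-group mean change at the same n per group. A size of 37 looks too small for an effect of under half an SD (0.3/0.63 = 0.476), and it is a size one would expect from a paired test in one group.

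This paragraph is the protocol's only justification for the trial's size, and it concerns the primary variable. If the stated power is wrong, a non-significant result could be read as stronger evidence against a 0.3 mM effect than the design can supply.

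**Working it through.** **Inputs, all from Protocol 6.1:** difference δ = 0.3 mM; SD σ = 0.63 mM, taken first as the SD of the within-person change; alpha 0.05; power 80%; 1:1 allocation. Both sidednesses are tried, because the sample-size sentence does not give one.

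**1. Reproducing 37.** One-sample (paired) t-test, standardised effect 0.3/0.63 = 0.476.
- Normal approximation, two-sided: n = (1.960 + 0.842)² × 0.63²/0.3² = 34.6.
- Exact noncentral t, two-sided: n = 36.6, rounded up to **37** (power 80.5% at 37 and 79.3% at 36).
- Exact, one-sided: 28.7, so 29.

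The stated figure is matched exactly by the two-sided one-sample test.

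**2. The test the protocol plans.** Two-sample t-test on the changes.
- Normal approximation: n per arm = 2 × (z₁ + z₂)² × σ²/δ², which is 2 × 34.6 = 69.2 (70) two-sided and 2 × 27.3 = 54.5 (55) one-sided.
- Exact t: 70.2, so **71 per arm** two-sided; 55.2, so **56 per arm** one-sided.

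**3. Power at the stated sizes.** Noncentrality = δ / (σ√(2/n)), with 2n − 2 degrees of freedom.
- n = 37: SE = 0.63 × √(2/37) = 0.146; noncentrality 2.05.
- n = 50: SE = 0.63 × √(2/50) = 0.126; noncentrality 2.38.

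| Per arm | Power for 0.3 mM, two-sided | One-sided | Difference with 80% power, two-sided | One-sided |
|---|---|---|---|---|
| 37 | 52% | 65% | 0.42 mM | 0.37 mM |
| 50 | 65% | 76% | 0.36 mM | 0.32 mM |

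**4. What would rescue 37.** Power depends on δ/σ, so the SD of change would have to be about 0.63 × 0.3/0.416 = 0.45 mM two-sided, or 0.63 × 0.3/0.368 = 0.51 mM one-sided. The protocol gives no such value.

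**5. If 0.63 mM is the SD of one measurement within a person.** With two unrestricted readings the SD of a change would be 0.63 × √2 = 0.89 mM. This is an upper bound here, because sections 3.3 and 3.4 admit only people with venous glucose of 6.1-6.9 mM at both the screening visit and visit 2, which narrows the baseline values. A simulation with that selection, a within-person SD of 0.63 mM and an assumed between-person SD of 0.1-0.8 mM (not given in the protocol) puts the SD of change at about 0.66-0.76 mM. The lower end applies when the mean of the screening and visit 2 values is the baseline, the upper end when visit 2 alone is. At 50 per arm the noncentrality is then 0.3/(0.66 × 0.2) = 2.27 down to 0.3/(0.76 × 0.2) = 1.97, which gives power of 61% down to 50% two-sided, or 73% down to 62% one-sided.

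**The case against.** **The trial recruits 50 per arm, not 37.** This is the strongest reply. The conclusions rest on the ITT analysis with missing values replaced by the latest available, so many dropouts would stay in the count. If a one-tailed test governs and everyone is analysed, power is 76%, less than 4 points short of 80%. That stands, and it limits the practical shortfall. It does not save the statement: 50 per arm is below 80% on either sidedness, and the extra 13 are presented as cover for dropouts. Section 6.1 also removes poor compliers from every analysis. A reader might infer that the trial has little better than an even chance of detecting 0.3 mM. With an SD of change of 0.63 mM, that describes only 37 per arm with a two-sided test.

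**The test is one-tailed.** In 6.1, one-tailed is attached to the before-after comparisons ("Participants will be analysed using intraindividual one-tailed comparisons before and after treatment"), and the between-arm t-test has no stated tail. A reader might infer a plain contradiction between a two-sided 37 and a one-tailed plan. The text is ambiguous rather than contradictory, and one-sided testing still needs 56 per arm.

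**The use of a one-sample formula is inferred.** True: it rests on the numerical match alone. The finding does not depend on it, since 37 per arm fails for the stated test whatever its origin.

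**The SD may be larger.** A reader might go further and quote 30% or 42% power at 37 per arm (38% or 51% at 50), using 0.89 mM. Those figures ignore the selection of baseline values at two visits and should be treated only as a floor on power.

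**Conclusion.** The point holds. With the protocol's own difference, SD and significance level, 37 per group does not give 80% power for the between-arm comparison, on either sidedness. The shortfall is 28 points two-sided or 15 points one-sided at 37 per arm (80 − 52 and 80 − 65), and 15 or 4 points at 50 per arm with no loss (80 − 65 and 80 − 76).

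These figures assume that 0.63 mM is the SD of the within-person change, that the changes are compared by an unadjusted two-sample t-test, and that the arms are equal in size and variance. If 0.63 mM is a single-measurement SD, power is lower, by an amount that depends on a between-person spread the protocol does not give.

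The documents do not show which formula was used, and they do not settle whether the between-arm test is one-sided or two-sided. The point is not something that can be left to a statistical analysis plan, because the protocol states a figure that its own inputs contradict.

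**What to change.** Correct the paragraph in section 6.1, with enrolment unchanged:

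1. State whether 0.63 mM is the SD of the within-person change or of a single measurement. If it is the latter, give the SD of change expected under the two-visit selection.
2. Name the between-arm comparison of changes as the primary test and fix one sidedness for it. The arithmetic does not dictate which.
3. Replace the claim of 80% power at 37 per group with the matching figures. For an SD of change of 0.63 mM, choose one line:
   - Two-sided 5%: 50 per arm gives 65% power for 0.3 mM and 80% for 0.36 mM; 37 evaluable per arm gives 52%, and 80% for 0.42 mM.
   - One-sided 5%: 50 per arm gives 76% power for 0.3 mM and 80% for 0.32 mM; 37 evaluable per arm gives 65%, and 80% for 0.37 mM.

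The cost is wording, plus a stated power that looks less favourable. No extra participants are needed for this correction. If the sponsor wants to keep 80% power for 0.3 mM at this SD, 71 (two-sided) or 56 (one-sided) evaluable participants per arm would be required, which is a separate decision.

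### The triglyceride subgroup analysis covers only the above-median half, so it cannot show that this half benefits more than the rest

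*Protocol*

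**What the plan says.** All of the relevant text is in Protocol section 6.1.

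- **The analysis:** "We will also make a subgroup analysis of participants with fasting triglycerides above median".
- **The reason for it:** an earlier study by the same group, described as "showing that BSE is particularly effective in individuals with increased triglyceride levels".
- **The question:** "we therefore want to investigate whether this subgroup of the population would benefit more from BSE".

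No test is named for the subgroup. For the primary variable the section says "Participants will be analysed using intraindividual one-tailed comparisons before and after treatment", and that these are "compared between the placebo and BSE arms using Student's t-test". I found no below-median analysis, between-halves contrast or interaction term anywhere in the protocol.

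Triglycerides are drawn at visit 2 before randomization (section 3.4) and again at visit 3 (section 3.7). Section 6.1 does not say which visit defines the median.

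**The concern.** The question is about a difference between two treatment effects, above and below the median. The analysis named estimates only one of them. If BSE works equally well across the triglyceride range, the upper half will often show a significant effect simply because BSE works. That result does not separate an equal benefit from an extra one.

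At stake is a statement about whom BSE suits best. Section 6.1 already describes a stronger effect at raised triglycerides in the group's previous BSE study, so a significant upper-half p-value could easily be taken as confirmation. Section 6.3 foresees publication in journals, for lay audiences and in the media.

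**Working it through.** **The plan's own figure.** The subgroup analysis has no calculation of its own. The only computed figure is "37 participants in each randomization group to detect a difference of 0.3 mM in fasting blood glucose between the groups at 80% power", with this SD: "The intra-individual standard deviation of fasting blood glucose is 0.63 mM". For two independent groups, a difference of 0.3 mM, SD 0.63 mM and alpha 0.05, the requirement is 55 per arm one-sided or 70 two-sided, so 37 is not reproduced. It does match a paired or one-sample two-sided t-test (36.6, rounded up). That is a separate matter, and nothing below depends on it.

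**Inputs from the protocol.** Effect 0.3 mM, SD 0.63 mM and alpha 0.05 (section 6.1); 50 per arm (section 3.9).

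**Assumptions.**
- The subgroup uses the same between-arm t-test on change as the primary variable.
- About half of each arm lies above the median: 50/2 = 25 per arm with no dropout, or 37/2 = 18.5, taken as 18, if numbers fall to the stated requirement.
- The SD of change is 0.63 mM as worded, or 0.63 × √2 = 0.89 mM if 0.63 belongs to a single measurement.

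**Step 1: upper half alone, true effect 0.3 mM in both halves.** SE = SD × √(2/n). Power is the chance that a noncentral t with 2n − 2 degrees of freedom and noncentrality 0.3/SE passes the critical value. For n = 25 and SD 0.63:

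- SE = 0.63 × √(2/25) = 0.178 mM; noncentrality = 0.3/0.178 = 1.68.
- One-tailed, critical value 1.677: 51%.
- Two-sided, critical value 2.011: 38%.

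| Per arm above median | SD of change (mM) | One-tailed | Two-sided |
|---|---|---|---|
| 25 | 0.63 | 51% | 38% |
| 18 | 0.63 | 40% | 28% |
| 25 | 0.89 | 32% | 21% |
| 18 | 0.89 | 26% | 17% |

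**Step 2: upper half significant, lower half not.** The halves are independent, so under equal effects this has probability p(1 − p). In the first row that is 0.51 × 0.49 = 25% one-tailed and 0.38 × 0.62 = 24% two-sided. In the last row, two-sided, it is 0.17 × 0.83 = 14%. Setting the two p-values side by side would therefore not answer the question either.

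**Step 3: the contrast that matches the question.** The difference between two independent subgroup effects has SE = SD × √(4/n) = 0.63 × √(4/25) = 0.252 mM. Under equal benefit its expectation is zero, so it is significant in about 5% of trials. A simulation of 20,000 trials with 25 per cell gave 5.2%, one- and two-sided.

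**Step 4: what that contrast can detect.** For a true difference of 0.3 mM between halves, by the normal approximation:

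- One-sided: Φ(0.3/0.252 − 1.645) = Φ(−0.45) = 32%.
- Two-sided: Φ(0.3/0.252 − 1.960) = Φ(−0.77) = 22%.
- With 18 per cell and SD 0.89, SE = 0.89 × √(4/18) = 0.42 mM, and power falls to 18% and 11%.
- With 25 per cell and SD 0.63, the difference detectable at 80% power is 0.252 × (1.645 + 0.842) = 0.63 mM one-sided, or 0.252 × (1.960 + 0.842) = 0.71 mM two-sided.

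**The case against.** **It is detail for the SAP.** Interaction terms, coding of the covariate and the visit that defines the median are usually settled there, and the SAP is not at hand. This holds for the coding and the choice of test. It does not dispose of the point, because the protocol states both a question and an analysis, and the second does not answer the first.

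**The upper-half result is not uninformative.** A reader might infer that it says nothing about extra benefit, or that significance there is to be expected whenever BSE works equally in everyone. Neither is supported. At 51% one-tailed it is a coin-flip at best, and two-sided it is less likely than not. The whole-group effect will also be reported. With equal halves that effect is roughly the average of the two, so the difference between halves is about twice the gap between the upper-half and overall estimates. What is missing is that contrast as a stated estimate with its uncertainty.

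**No targeting claim is written.** A reader might infer that the sponsor plans to claim greater benefit from the above-median p-value. Section 6.1 speaks only of wanting to investigate, and the subgroup appears in neither the objectives nor the effect variables (sections 4.1 to 4.3). The risk lies in how the result may be read.

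**A prespecified median split is not an error.** This stands. Continuous or log-transformed triglycerides would be a modelling preference, and would bring shape assumptions of their own.

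**The right contrast has little power.** True, and it must be said in the plan. Low power is a reason to show both halves with intervals, and no reason to test only one.

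**Conclusion.** The point holds as a mismatch, within one paragraph of section 6.1, between a comparative question and a one-half analysis. Under equal benefit of 0.3 mM in both halves, the above-median comparison is significant in 26–51% of trials one-tailed and 17–38% two-sided, against about 5% for an interaction test. The upper ends assume 25 per arm above the median and 0.63 mM as the SD of change. The lower ends assume 18 per arm and 0.89 mM. All assume that the primary t-test is carried over to the subgroup.

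A reader might extend this to the primary result; the documents give no ground for that, since the subgroup enters neither the sample size nor the primary comparison. Nor do they show that the median would be taken from visit 3 values. The visit is simply not named, and naming visit 2 removes the doubt. The change is worth making, but it bears only on the subgroup conclusion.

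**What to change.** Amend the subgroup paragraph of section 6.1 to state the following:

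1. Participants are divided at the median of visit 2 (pre-treatment) fasting triglycerides.
2. The BSE–placebo difference in change in fasting glucose is reported with a 95% CI in both halves.
3. The difference between these two effects (the arm-by-triglyceride-group interaction) is estimated with its 95% CI, in the same analysis population as the primary comparison. Because the primary analysis is a t-test, this is a separate contrast and does not extend an existing model. An analysis with continuous triglycerides may be added as a sensitivity analysis.
4. The analysis is exploratory. No claim of greater benefit rests on the above-median p-value alone, and a non-significant interaction is not read as equal benefit.

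The cost is a change of wording and one further contrast, with no new data, since triglycerides are already measured at visit 2. The downside is that a claim of greater benefit becomes harder to make. At this sample size the interval for the contrast will be wide: with SE 0.252 mM, about ±1.96 × 0.252 = ±0.49 mM at best.
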